## Abstract

**Background:**

Zambia is a sub-Saharan country with one of the highest prevalence rates of HIV, currently estimated at 14%. Poor nutritional status due to both protein-energy and micronutrient malnutrition has worsened this situation. In an attempt to address this combined problem, the government has instigated a number of strategies, including the provision of antiretroviral (ARV) treatment coupled with the promotion of good nutrition. High-energy protein supplement (HEPS) is particularly promoted; however, the impact of this food supplement on the nutritional status of people living with HIV/AIDS (PLHA) beyond weight gain has not been assessed. Techniques for the assessment of nutritional status utilising objective measures of body composition are not commonly available in Zambia. The aim of this study is therefore to assess the impact of a food supplement on nutritional status using a comprehensive anthropometric protocol including measures of skinfold thickness and circumferences, plus the criterion deuterium dilution technique to assess total body water (TBW) and derive fat-free mass (FFM) and fat mass (FM).

**Methods/Design:**

This community-based controlled and longitudinal study aims to recruit 200 HIV-infected females commencing ARV treatment at two clinics in Lusaka, Zambia. Data will be collected at four time points: baseline, 4-month, 8-month and 12-month follow-up visits. Outcome measures to be assessed include body height and weight, body mass index (BMI), body composition, CD4, viral load and micronutrient status.

**Discussion:**

This protocol describes a study that will provide a longitudinal assessment of the impact of a food supplement on the nutritional status of HIV-infected females initiating ARVs using a range of anthropometric and body composition assessment techniques.

**Trial Registration:**

Pan African Clinical Trial Registry PACTR201108000303396.

## Background

Zambia is among the five countries in sub-Saharan Africa with the most serious HIV/AIDS epidemic [1]. In 2007, the HIV prevalence rate in adults was reported to be 14%, a slight but non-significant decrease from 16% in the 2001-2002 (Zambia Demographic Health Survey) [2]. Zambia also suffers from high rates of both macro- and micro-nutrient malnutrition. Indicators of nutritional status in children under five years of age show the prevalence of stunting, underweight and wasting at 45%, 15% and 5%, respectively. The prevalence of vitamin A deficiency and anaemia in the same age group is 54.1% and 52.9%, respectively [2-4]. Malnutrition compromises immunity to infectious diseases, which in turn aggravates malnutrition. The so-called malnutrition infection complex (MIC) is a well known phenomenon and the presence of HIV has made the situation worse. HIV/AIDS also drives household vulnerability to food insecurity, which contributes to households not having access to adequate food to meet the daily nutrient requirements for individuals to lead active and healthy lives [5].

Following the first diagnosed AIDS case in Zambia in 1984, the Government has put in place a number of strategies and interventions to fight the epidemic [6]. These interventions include preventive approaches to reduce new cases of HIV/AIDS infection and the provision of free ARV treatment [7]. To achieve the full benefit of ARV treatment, adequate nutrition is essential, therefore the government promotes good nutrition and in particular, HEPS is provided to PLHA, including those on ARV treatment. Commonly, HIV-infected individuals have reduced food intake due to the effect of the HIV infection compounded by secondary opportunistic infection. This has a marked effect on appetite leading to reduced food intake and consequently, to weight loss [8]. Weight loss in PLHA is dissimilar to that observed in severely malnourished individuals, as FFM rather than FM diminishes with the HIV infection. With the advent of ARV treatment, multiple additional nutritional changes which lead to obesity and the metabolic syndrome have been observed [9].

Typically, measurement of body weight is the nutritional assessment approach used to monitor health outcomes in resource-limited countries, with gain in absolute weight being the desired short-term outcome. Less common is the use of other anthropometric approaches such as circumference and skinfold thickness measurement, or objective body composition techniques. Bioelectrical impedance analysis (BIA) is a quick, non-invasive and relatively inexpensive body composition assessment technique [10,11] suitable for routine clinical use in the developing world. Skinfold anthropometry has been used to estimate body composition in HIV-infected persons using predictive equations however; as equations are population-specific, they need to be validated against a gold standard method before being used on another population [12].

This study aims to measure the impact of HEPS on the nutritional status and body composition of HIV-infected people who commence ARV treatment, over a 12-month period. In this study, body composition will be assessed using the stable isotope dilution technique to quantify TBW and subsequently FFM, along with body height, weight, BMI, skinfold and circumference measurements plus BIA.

Food intake and micronutrient status will also be assessed in the study population. This is based on the premise that the prevalence of macronutrient and micronutrient malnutrition, particularly vitamin A and iron, worsens with the HIV/AIDS epidemic. Further, as CD4 counts and viral load are important biomarkers of health status in this population, they will also be measured.

## Methods/Design

### Study design

This is a community-based controlled and longitudinal study. The study population will be comprised of HIV-infected females commencing ARV treatment at two Lusaka Urban clinics, Matero Reference Clinic (MRC) and Matero Main Clinic (MMC). The study participants will be allocated to either the experimental group and receive HEPS or control group and not receive HEPS. Participants will be randomly assigned to either group by the sister-in-charge at each clinic. Data will be collected at four time points across the 12-month study: baseline (0 months), 4-months, 8-months and 12-months follow-up. The study protocol has been approved by the University of Zambia Research Ethics Committee (approval ref 017-02-07).

### Recruitment

Participants will be recruited to the study from women who report to each clinic for care and support after being diagnosed as HIV-positive at a Voluntary and Counselling Treatment (VCT) centre in Lusaka. The clinics will collect blood samples for CD4 count, viral load and liver function tests from each study participant and subsequent appointment times to collect their results will be given. Blood samples collected in all government clinics in Lusaka are analyzed at the Centre for Infectious Diseases Research Laboratories in Lusaka. Upon receipt of results the sister-in-charge at each clinic will screen the results and identify those individuals considered to be eligible to commence ARV treatment based mainly on a CD4 count of 350 cells/μL or less.

Using a tracking system which consists of the participant's residential address and telephone number (or that of their spouse or guardian), eligible participants will be reminded of their clinic appointments. For those who do not have telephone contacts, a clinic staff member will visit them at their respective homes to inform them of their appointment and the need to report to the clinic and the Sister-in-Charge for ART. The sister will then invite each client one by one and explain the nature of the study. Once the client agrees to participate they will be asked to sign a consent form in duplicate or if they are unable to write, they will provide a thumb print. The Sister-in-Charge will sign as a witness. The original copy will be filed at the clinic while the duplicate copy will be stored by the Principal Investigator (PI) in a locked filing cabinet at the project office.

Once the client has consented to the study a project ID number will be assigned and the PI will meet with each individual to work through the information sheet in detail. During this period, each client is provided with another opportunity to clarify any issues or concerns before embarking on the study. Trained nursing and project staff will take routine measurements such as blood pressure and body temperature and also collect a urine sample for a pregnancy test. This will be followed by a full physical examination by a medical practitioner. Once the client has been certified as eligible to commence ARV treatment and meets all inclusion criteria she will be enrolled as a study participant.

Participants will be eligible if they are HIV-positive with CD4 count 350 cells/μL or less; are commencing ARV treatment; female aged 20-40 years; not mentally challenged and agree to participate in the study. Participants will be ineligible if clinically unstable or with other medical conditions (e.g., elevated creatinine), which will prevent them from commencing on ARV treatment, if they are pregnant or plan to fall pregnant during the study.

### Allocation to study groups

On the day of recruitment (baseline) after completing all body composition assessments and physical examination, the sister-in- charge will cut pieces of papers, equal to the number of participants enrolled that day. Half of the papers will bear the word 'Soya' while the other half will have 'No Soya' written on them. The papers will be folded several times to conceal the writing and then mixed. Each participant will be asked to pick one and read loud for the sister-in-charge to record the group assignment in the study registry book.

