### Recruitment and training of field staff

Six nurses, three from each of the two selected study site clinics, and two medical practitioners, one from each clinic, will be recruited and trained as field staff across two comprehensive training sessions. The aim of the first training session will be to introduce the anthropometric and body composition techniques and methodologies using both theory and practical demonstrations. In addition, a pre-test will be conducted at one of the clinics using 10 volunteer students from the Natural Resource Development College (NRDC) in Lusaka who are undertaking a food and nutrition diploma course. Ten students will be selected for the pre-test to provide the opportunity for a real world practical application of their theoretical work in class as this is the anticipated maximum number of participants likely to be recruited in a day.

The second training session will involve on-site training for the field staff at the respective clinics selected for the study. The training will be conducted a week prior to commencement of the recruitment of participants and baseline data collection. The aim of the on-site training will be to acquaint field staff with the sequence of events to be followed during data collection, have a final hands-on practice of the techniques and work out other logistical issues including space, laboratory and cafeteria facilities. A total of 50 female volunteer students from NRDC will be used as participants, 10 per day with three days training to be conducted at Matero Reference Clinic and two days at Matero Main Clinic. Students will be given appointment times to report to the clinics and will be refunded for transport expenses. However, measurements during the on-site training will be limited to body composition assessment. Physical examination by the medical practitioner, gravidex test, and collection of blood for assessing total blood count, CD4 counts, viral load and micronutrient analysis will not be undertaken. Similarly, tests relating to HIV/AIDS status and counselling will not form part of the pre-test.

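### The daily slip draw cannot be carried out when an odd number of women is enrolled, and no rule governs the extra slip

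*Protocol article*

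**What the plan says.** The Study design section gives the allocation to one person per clinic: "Participants will be randomly assigned to either group by the sister-in-charge at each clinic". The section Allocation to study groups sets out how she does it. On the day of recruitment, "after completing all body composition assessments and physical examination", she cuts slips "equal to the number of participants enrolled that day. Half of the papers will bear the word" Soya, the other half No Soya. The slips are folded and mixed. "Each participant will be asked to pick one and read loud for the sister-in-charge to record the group assignment" in the study registry book.

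The Recruitment section shows that the same sister-in-charge screens the laboratory results for eligibility, invites the women and witnesses consent: "The sister will then invite each client one by one and explain the nature of the study".

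On daily numbers, the article offers only a remark made when sizing the training pre-test at 10 students: "this is the anticipated maximum number of participants likely to be recruited in a day". It sets no minimum, does not require an even count, does not carry a slip over to another day, and gives no instruction for an odd count.

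**The concern.** The rule imposes two conditions: as many slips as women, and equal numbers of each label. Both can be met only when the day's count is even. On any other day someone must decide the label of one slip. By the text that task falls to the sister-in-charge, since she alone makes the slips. She makes them after she has screened and recruited the women and after they have been examined, so the label is settled when the day's group is already known to her.

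The arms differ visibly and in value. One receives 10 kg of food a month plus transport money at each collection; the other receives detergent paste and soap every 4 months. Nutritional status and body composition are the primary outcomes. Random allocation is what protects that comparison, and an unspecified step in the hands of the recruiter weakens the protection on the days it affects. On a day with one woman it removes it.

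**Working it through.** The plan states no figure here to reproduce, so the check applies its rule literally and then asks how often it fails.

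**Step 1. Which daily counts work.** Input: n slips for n women, n/2 per label (Allocation to study groups). For n = 2, 4, 6, 8 or 10 the rule works and P(Soya) = 1/2. For odd n, n/2 is not a whole number. With n slips the closest split has (n+1)/2 of one label and (n−1)/2 of the other, so P(Soya) = (n+1)/2n if the extra slip is labelled Soya, and (n−1)/2n if it is not.

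| Women that day | n/2 | P(Soya), extra slip Soya | P(Soya), extra slip No Soya |
|---|---|---|---|
| 1 | 0.5 | 1 | 0 |
| 3 | 1.5 | 0.667 | 0.333 |
| 5 | 2.5 | 0.600 | 0.400 |
| 7 | 3.5 | 0.571 | 0.429 |
| 9 | 4.5 | 0.556 | 0.444 |

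**Step 2. What is left to discretion.** For n of 3 or more, the folded slips are mixed and picked by the women, so every woman that day has the same probability; only that common probability depends on the label. For n = 1 there is one slip, the draw contains no randomness, and the label is the assignment.

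**Step 3. How often (assumption).** The documents give no distribution of daily numbers. Suppose the count per clinic-day is Poisson with rate λ, days with no enrolment are dropped, and the cap at 10 is ignored. Then:

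- share of recruiting days that are odd = (1 + e^−λ)/2
- share of women enrolled alone = e^−λ
- mean women per recruiting day = λ/(1 − e^−λ)

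| λ | Odd days | Women enrolled alone |
|---|---|---|
| 1 | 68% | 37% |
| 2 | 57% | 14% |
| 3 | 52% | 5.0% |
| 5 | 50% | 0.7% |

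If instead every count from 1 to 10 were equally likely, 50% of days would be odd and 1/55 = 1.8% of women would be enrolled alone.

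For 200 women:

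- λ = 3: mean 3/0.950 = 3.16 per day, so about 63 days, about 33 of them odd, and 200 × 0.050 = 10 women enrolled alone.
- λ = 5: mean 5/0.993 = 5.03 per day, so about 40 days, about 20 of them odd, and 200 × 0.0067 = 1.3 women enrolled alone.

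**Step 4. Upper bound on imbalance.** If all 20 extra slips at λ = 5 went to one arm, the split would be (200 + 20)/2 : (200 − 20)/2 = 110:90. Its efficiency relative to 100:100 is 4 × 110 × 90/200² = 0.99. Exactly three women every day would give 66 extra slips and at most 133:67, with efficiency 4 × 133 × 67/200² = 0.89.

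**Step 5. Effect of a chance rule.** If a fair coin labels the extra slip, P(Soya) = ½ × (n+1)/2n + ½ × (n−1)/2n = 1/2 for every odd n, including n = 1.

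**The case against.** The article is condensed, and the full protocol may say what happens on odd days. Nor does the text say that the sister-in-charge chooses the label as she likes; she could toss a coin. Both points are fair, and no misuse is shown. But the article describes the procedure step by step, and two of its stated conditions conflict for half of the counts from 1 to 10. That is a fault in a stated rule rather than an omitted detail. If the full protocol has a rule for odd days, quoting it would close the point.

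Three stronger readings are tempting and are not supported:

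- **Food can be steered to the neediest women.** With three or more women the sister-in-charge could change only the day's ratio, not who draws which slip. To bias the comparison she would have to tilt ratios according to how ill a whole day's group is. Control over an individual arises only when a woman is enrolled alone.
- **Slips read aloud make the last draws predictable, and so biased.** Enrolment and baseline assessment are complete before the slips are cut, so this knowledge cannot affect who enters. Calling women in a chosen order does not help either: the proportion of Soya slips among those remaining has a constant expectation under drawing without replacement, so a woman's chance on an even day stays 1/2 whenever she is called.
- **There is no independent record.** The documents do not show this. Assignments go into a registry book, and the principal investigator or project staff check completed forms at the clinic (Data management and entry).

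Imbalance in numbers is also a minor harm: 110:90 costs about 1% of efficiency.

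**Conclusion.** The point holds in a limited form. It is certain, by arithmetic alone, that the rule cannot be followed for an odd count and that a single slip leaves nothing to draw. That the sister-in-charge settles the label is an inference from her sole role in making the slips and from the absence of any rule.

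The reach depends on daily numbers that the documents do not give. At an assumed average of about 3 to 5 women per clinic-day, roughly half the days have an allocation ratio open to discretion, and about 1% to 5% of women (roughly 1 to 10 of 200) would be assigned without any draw. Slower recruitment raises this, to about 37% of women at a Poisson rate of 1. No bias in an outcome can be estimated from the documents, and none is claimed. The correction is still worth making, because it is cheap and the gap lies in the randomisation itself.

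**What to change.** Replace the daily slips with sequentially numbered, sealed opaque envelopes, one series per clinic. They should be prepared in advance from a computer-generated list with permuted blocks of varying size, by project staff not involved in recruitment. As the principal investigator goes through the information sheet with each woman, this should be someone else. Open the envelopes in number order after baseline assessment and log each number and time. Blocks then run across days, so an odd count needs no decision and a woman enrolled alone is randomised like any other.

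The cost is about 200 envelopes, one list per clinic and some project-office time. The small downside is that women no longer see a public draw.

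If the public draw is to be kept, the minimum is one added sentence fixing a chance rule for the odd slip in advance, for example a witnessed coin toss whose result is recorded. Every woman then has a 1/2 chance, including one enrolled alone.

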### Intervention/experimental group

A total of 120 kg of the food supplement will be given to each participant in the intervention or experimental group during the 12-month study period. To ensure a fresh supply of the food supplement and to minimise sharing or selling, the participants will be given 10 kg of the food supplement, enough for 30 days, and will be asked to collect 10 kg each month from the clinic. Each time the participant travels to collect the food supplement they will be given Zambian kwacha (ZMK) equivalent to approximately US$3 to cover the cost of transport from their home to the clinic. HEPS is a mixture of extruded maize meal and soya flour to which sugar and a vitamin-mineral mix have been added. Porridge is the common form in which HEPS is consumed. The participants will be given instructions on how to prepare the porridge from the HEPS and will be advised to consume it at least two times a day. In addition, they will receive further advice on the importance of good nutrition at the same time of taking ARV medication.

### Control group

Participants in the control group will not receive any food supplement but instead will receive a box of detergent paste and a packet of toilet soap once every 4 months at each scheduled follow-up visit. This group will also receive the same nutritional advice as the experimental group including medication.

### Training of project staff

The International Atomic Energy Agency (IAEA) will provide Fellowship training for two project team members, the PI and a senior laboratory technician. Training in body composition measurement techniques will be undertaken at Queensland University of Technology, Brisbane, Australia. The trained project staff will further refine their skills prior to training the field staff by completing pilot testing on 20 volunteer participants recruited from amongst the staff members at the research institution. This will assist in the preparation of a locally adapted training manual for subsequent use in the training of all field staff.

The use of BIA, skinfold thickness, circumference and isotope dilution techniques to assess nutritional status is not common in Zambia. Therefore, prior to implementing the field work a high level advocacy and awareness meeting for policy makers in public, private and international organisations dealing with nutrition and health will be organised to seek their support. Mixed presentations covering nutritional challenges, the consequences of HIV infection, interventions, traditional nutrition assessment tools and their limitations and state-of-the-art techniques will be made. Presenters will include renowned health practitioners, nutritionists, research scientists from various arms of government, and a technical expert from the IAEA.

### Recruitment and training of field staff

Six nurses, three from each of the two selected study site clinics, and two medical practitioners, one from each clinic, will be recruited and trained as field staff across two comprehensive training sessions. The aim of the first training session will be to introduce the anthropometric and body composition techniques and methodologies using both theory and practical demonstrations. In addition, a pre-test will be conducted at one of the clinics using 10 volunteer students from the Natural Resource Development College (NRDC) in Lusaka who are undertaking a food and nutrition diploma course. Ten students will be selected for the pre-test to provide the opportunity for a real world practical application of their theoretical work in class as this is the anticipated maximum number of participants likely to be recruited in a day.

The second training session will involve on-site training for the field staff at the respective clinics selected for the study. The training will be conducted a week prior to commencement of the recruitment of participants and baseline data collection. The aim of the on-site training will be to acquaint field staff with the sequence of events to be followed during data collection, have a final hands-on practice of the techniques and work out other logistical issues including space, laboratory and cafeteria facilities. A total of 50 female volunteer students from NRDC will be used as participants, 10 per day with three days training to be conducted at Matero Reference Clinic and two days at Matero Main Clinic. Students will be given appointment times to report to the clinics and will be refunded for transport expenses. However, measurements during the on-site training will be limited to body composition assessment. Physical examination by the medical practitioner, gravidex test, and collection of blood for assessing total blood count, CD4 counts, viral load and micronutrient analysis will not be undertaken. Similarly, tests relating to HIV/AIDS status and counselling will not form part of the pre-test.

